#### Ecological momentary assessment (EMA).

Participant’s current state and behaviors will be collected using a customizable software (LifePak, LifeData Corporation, Marion, IN). This software is compatible with both Apple and Android iOS delivered phone notifications as reminders, and study surveys will be completed within the app. Questions occur in the same order for all surveys and are provided as supplementary material (S2–S4 Tables) and a detailed account of constructs is provided in Fig 1. Participants will receive six surveys, including four signal-contingent and two fixed surveys (i.e., available for a fixed time period), through the app each day for 14 continuous days as performed by others measuring physical activity [20]. Signal-contingent surveys occurred randomly within fixed 3-hour windows (8:00am–11:00am, 11:00am-2:00 pm, 2:00 pm-5:00 pm, and 5:00–8:00 pm) and expire 45 minutes after the initial reminder. The two fixed surveys include the morning and evening survey; the morning survey will be available for four hours (8:00am-12:00 pm), and three hours for the evening survey (5:00–8:00 pm). These schedules may be shifted for non-traditional schedules, such as shift work, to ensure participants are available to answer these questions during their waking hours. Participants will be provided with three reminders for signal-contingent surveys, including the initial reminder, and reminders at 15-minutes and 30-minutes, if necessary. Participants will be sent reminders for the morning and evening surveys every hour, if necessary. Sampling time frames and prompt strategies were informed by past EMA studies [21,22]. Participants will be expected to complete at least one morning survey and two within-day surveys (~50%) for 5-days [23], with an additional incentive for 7-days in a row as conducted in our preliminary EMA studies.

#### Primary exposures.

**Variability in stress and coping:** In the morning survey, morning stress and coping will be assessed using questions based on the Daily Health Diary as assessed in past EMA studies [23,24], their own current stress and their perceived ability to cope with stress. Participants will be prompted to indicate the current stress, with response options ranging from 0–10 and 10 indicating higher stress. Participant coping will be queried with a similar question on their ability to manage stress right now, with the same response options and a higher score indicating a higher ability to manage stress.

**Variability in affect:** During signal-contingent surveys, participants will answer a set of five brief questions including positive and negative affective response. Then, participants will complete 5-questions based on how they are currently feeling positive and negative affect based on the Positive and Negative Affect Scale (PANAS), a validated scale which has been adapted in other EMA studies of affect [10,24,25]. These questions will be asked in the same order and are based on previous EMA studies [6,23,26], with response options ranging 1–4, with higher indicating more prevalent feelings of the emotion. An average of the two positive affect questions and three negative affect questions will be calculated. The average positive affect score will be compared for variability in affect.

#### Other stress-related states, and health behaviors.

As shown in Table 1, morning, signal-contingent, and evening surveys will assess other relevant considerations. The morning survey includes 16 questions, ending with the two questions that assess stress and coping. Participants will be asked, based on the previous night, how many hours of actual sleep they received, their bedtime and wake-time, and overall sleep quality. These questions are adapted from the Pittsburgh Sleep Quality Index, which is validated in adults [27]. This is followed by two questions on accelerometer and saliva compliance and then questions related to coping with stress and cravings the previous day. Cravings will be assessed using an adapted momentary scale of the Food Cravings Inventory (FCI). The FCI is questionnaire queries five different subscales including high fat foods, sweets, carbohydrates/starches, fast foods, and fruits and vegetables; this scale has been validated in adults [28]. FCI responses are via a 5-point scale, with higher scores indicating more frequent cravings. In the momentary question, we will ask how often they felt cravings for each of the 5-main items, with similar Likert scale responses. For example, they will be asked how frequent they craved carbohydrates/starches during the day. They will be asked if they indulged in cravings, and if so, which of the five craving groups with check box option.

**Table 1 pone.0357572.t001:** Daily Schedule of Ecological Momentary Assessment Surveys sent to participants for 14-days.

Construct	Morning Survey (8a-12p)	Period 1 (8a -11a)	Period 2 (11a -2p)	Period 3 (2p-5p)	Period 4 (5p-8p)	Evening Survey (6p-10p)
Sampling	Fixed	Random	Random	Random	Random	Fixed
*Stress and stress-related concepts*						
Acute Stress	x	x	x	x	x	x
Coping Mechanisms	x					x
Affect		x	x	x	x	
Chaos/ Disorder		x	x	x	x	x
Context		x	x	x	x	
*Health Behaviors*						
Diet	x					x
Cravings	x					x
Physical Activity						x
Sleep	x					
Survey Burden						x

Participants will also be surveyed about accelerometer wear at night and salivary cortisol collection in the morning survey, and accelerometer wear during the day will be queried in the evening survey.

The signal contingent survey includes eight questions total. First, participants will be asked a 1-question item to assess routine and disorder within the moment adapted from the Confusion, Hubbub and Order Scale [29]. Then, participants will complete the PANAS scale as described previously. Finally, participants will be queried where they are located (e.g., home, work) and who they are with (alone, friends, etc.) to address context.

The evening survey includes 11 questions. First, participants will report overall daily stress, and then indicate transient stressors, including home, school, job, conflicts with partner or children, and financial stress using checklist options [30]. This will be followed with four questions related to home chaos that demonstrated high validity and reliability in a previous adult sample (Cronbach’s alpha = 0.79, re-test reliability, r = 0.82) [31]. Then, participants will be asked if they engaged in moderate to vigorous physical activity, and if so, how many minutes during the day. These questions were based off primary questions the Godin-Shephard leisure questionnaire which has been validated in adults [32]. Survey burden will be assessed using a 1-item question at the end of the survey. Participants will be queried to the burden of completing the survey that day, with a scale of 1–5, with a higher score indicating it was very burdensome.

#### Stress-related states and health behaviors.

Momentary measures, demographics and attendance, stress and related states, and health behaviors will be assessed across Visits 1–4 (Table 1).

#### Primary outcome: Weight.

Participants’ height (cm) and weight (kg) will be objectively measured by a trained research assistant using standard operating procedures, such as shoes removed, with a mounted stadiometer and portable scale. Measurements will be taken in duplicate and an average was used. If the measurements differed by more than 0.5 units, then a third measurement was taken. Body mass index (BMI, weight/height^2^, kg/m^2^) will be calculated. Weight at Visits 2−4 will be subtracted from Visit 1 (Week-0) to calculate change in weight.

#### Secondary outcome: Physical activity and sleep.

Physical activity will be using an Actigraph GT3X+ accelerometer (Actigraph, LLC, Pensacola, FL) recorded at 50hz sampling rate and placed on the wrist of the nondominant arm for the entirety of the EMA protocol, including overnight. The GGIR algorithm will be used to detect non-wear time then equate remaining time as sleep by wear angle [33]. Days with >10 hours of awake wear and ≥20 hours of total wear time (awake and sleep) will be considered a valid day. GGIR version 3.2.6 will be used to process metrics using the remaining raw accelerometer data [33–35]. The Euclidian Norm Minus One (ENMO), the vector magnitude of three axes minus 1 g will be calculated and used to classify physical activity level. Activity will be classified as inactive (0–39 mg), light ([LPA], 40 mg ≤ ENMO <100 mg), and MVPA (ENMO ≥100 mg) [36]. Due to possible random wrist movement, bouts of ≥1 minute where 80% of the activity was classified as MVPA were used as performed by others [37]. Variables will be summarized for each participant for available days (minutes/day). In addition to device-based measures, a best practice is to also include questionnaires [38]. For physical activity intensity, participants will also complete the Godin-Shephard Leisure Time Physical Activity Questionnaire to assess physical activity within the past week. This questionnaire is validated within adults [32]. As for sleep, participants will report their recent sleep habits using the Pittsburgh Sleep Quality Index, which is validated in adults [27]. Participants will report sleep quality, sleep duration, and daytime dysfunction.

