### Analytical approach

#### Aim 1: Examine the association between variability in individual stress and weight change.

For hypothesis 1a, that high variability in daily stress will be related to less weight loss, linear regression will examine week-0 average and change frequency in daily stress (morning survey) with weight change at week-12 (visit 3) and week-26 (visit 4). For hypothesis 1b, that high variability in daily stress will be related to less physical activity and sleep, multi-level models with logit link function (and binomial distribution) will be used to examine association between week-0 morning stress and same day MVPA and sleep, with an interaction of time/day*morning stress. For exploratory analyses, we will examine the associations of daily stress with MVPA and sleep at other time points (week-6, week-12, and week-26), lagged day effects of stress (i.e., stress on day 1 influencing MVPA and sleep on day 2) to preserve temporal ordering and considering inverse probability weighted marginal structural models, and the outcome of weight change at week-6.

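### The single accelerometer valid-day rule can count a night as valid for sleep with up to 4 hours of it unrecorded; a sleep-specific night criterion should be added

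*Protocol article*

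**What the plan says.** All device processing is described in one section of the protocol article, "Secondary outcome: Physical activity and sleep". The accelerometer is to be "placed on the wrist of the nondominant arm for the entirety of the EMA protocol, including overnight". On processing, the section states: "The GGIR algorithm will be used to detect non-wear time then equate remaining time as sleep by wear angle". It then gives its only validity criterion: "Days with >10 hours of awake wear and ≥20 hours of total wear time (awake and sleep) will be considered a valid day". Device variables are summarised per participant, in minutes per day, over the available days. The section gives no minimum for wear during the sleep period and no imputation of unworn time.

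The Aim 1 analysis for Hypothesis 1b uses day-level values. A multi-level model will "examine association between week-0 morning stress and same day MVPA and sleep".

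Three other passages bear on night wear:
- The morning survey asks "how many hours of actual sleep they received, their bedtime and wake-time, and overall sleep quality".
- The note to Table 1 says that the morning survey also asks about device wear at night.
- The data management plan says that non-wear and implausible values will be sought through wear logs and quality control.

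None of the three sets a threshold for a usable night.

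**The concern.** A total-wear threshold measures how complete the 24 hours are. It does not measure how complete the sleep period is. Sleep fills roughly a third of the day, so a loss that is small against 24 hours can be large against the night. Because non-wear is taken out first and sleep is sought only in what remains, hours with the device off cannot be recovered as sleep. A participant who takes the device off part-way through the night can therefore have a valid day with a short sleep value that reflects wear, not sleep.

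This differs in kind from missing data. The data management plan foresees mixed models that tolerate incomplete repeated measures under a missing-at-random assumption. A truncated night is not incomplete in that sense: a value is present, and it is too low. Such models would take it at face value. What is at stake is measurement error in device-measured sleep, one of the two secondary outcomes and one of the two responses in Hypothesis 1b.

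**Working it through.** The plan sets the wear thresholds and does not derive them, so there is no figure of its own to reproduce. The check applies the rule as a logical test.

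**Inputs**
- From the secondary-outcome section: awake wear must exceed 10 h, and total wear must be at least 20 h. At most 24 − 20 = 4 h may be unworn.
- From the same section: sleep is classified only from time left after non-wear is removed.
- Assumed: sleep length S, which the documents do not give, varied from 5 to 10 h. Waking time is 24 − S. Each day is taken to contain one whole night.

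**Step 1. Least night wear accepted with full waking wear**

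Least sleep wear = 20 − (24 − S) = S − 4. The largest unrecorded share of the night is therefore 4/S.

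| Sleep S (h) | Waking wear (h) | Least sleep wear accepted (h) | Largest unrecorded share |
|---|---|---|---|
| 5 | 19 | 1 | 80% |
| 6 | 18 | 2 | 67% |
| 7 | 17 | 3 | 57% |
| 8 | 16 | 4 | 50% |
| 9 | 15 | 5 | 44% |
| 10 | 14 | 6 | 40% |

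For S = 8, 16 h awake + 4 h asleep = 20 h. The day is valid with half the night unrecorded. A loss of half the night or more is possible whenever S is 8 h or less.

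**Step 2. Whole night off**

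With 16 h awake and 0 h asleep, total wear is 16 h, which is below 20, so the day is rejected. The same holds for every S from 5 to 10 h. The exposure is to partly worn nights.

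**Step 3. What the 20-hour condition does for MVPA**

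With full sleep wear at S = 8, the least awake wear accepted is 20 − 8 = 12 h. At most 4 of 16 waking hours (25%) can then be unrecorded. If sleep wear is below 10 h, total wear of 20 h already implies more than 10 h awake, so the 10-hour condition adds nothing. An awake-wear-only rule of more than 10 h would allow almost 16 − 10 = 6 of 16 waking hours (37.5%) to be unrecorded.

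**Step 4. Sensitivity to the definition of a day**

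The article does not say whether a day runs midnight to midnight or wake to wake. On calendar days, one night draws on the allowances of two days. With full waking wear, an 8-hour night starting 1 h before midnight could lose 1 + 4 = 5 h (63%) with both days valid. A night starting 2 h before midnight could lose 2 + 4 = 6 h (75%). The 50% for an 8-hour night is therefore not an upper bound under every definition.

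**The case against.** The strongest reply is that a 24-hour completeness rule suits a 24-hour wear protocol, and that the loss shown is a worst case. It needs full waking wear and removal for just the permitted time, and every waking hour off reduces the permitted night loss by an hour. Overnight wear is instructed, night wear is asked about each morning, and logs are reviewed. Self-reported sleep, nightly and by the Pittsburgh index, could expose a large discrepancy. This stands as a limit on frequency. It does not remove the gap, because none of these steps says when a night's device sleep is to be discarded.

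A second reply is that night-level cleaning may sit in a full plan that is not shown. That is possible. However, the article itself fixes a validity rule in the section for both outcomes, and nothing in it points to a further rule for nights.

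Two stronger readings are tempting, and the document does not support either.
- A reader might infer that the rule is also wrong for MVPA, because it rejects a day with all 16 waking hours recorded and the device off at night. It does reject that day. But the 20-hour condition is also what holds waking loss to 4 of 16 hours, and dropping it would allow almost 6. This is a trade-off, not an error.
- A reader might infer that the rule would create the hypothesised link between stress and sleep, since device removal could go with restlessness or stress. The document has no wear data and no evidence of such a link. An illustration such as two nights each short by 240 minutes in 14, which is 2 × 240 / 14 = 34 min/day, rests on an invented frequency. It describes a 14-day mean, whereas Hypothesis 1b is a day-level model with a logit link, so it does not give the bias in that coefficient.

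**Conclusion.** The point holds for sleep and is minor. As written, the rule can count a day as valid for sleep with up to 4 hours of the night unrecorded, which is 40% to 57% of a night of 10 to 7 hours and 50% at 8 hours. The shortened value can be analysed as short sleep. This rests on four assumptions: full waking wear, the assumed sleep lengths, no imputation of unworn time (none is stated), and device-measured sleep as the Hypothesis 1b response. The number of affected nights, their relation to stress, and the size or direction of any bias in the Hypothesis 1b estimate cannot be determined. The primary weight analysis is not affected.

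**What to change.** Keep the stated rule as the primary valid-day rule for MVPA. Add a separate night flag for sleep: score device sleep only if the device was worn for nearly all of the sleep window, and otherwise set sleep to missing for that night. A threshold of at least 90% is an example; the document does not supply one.

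Take the window from the bedtime and wake-time in the morning survey. Where that survey is missing, use device-detected times or the wear logs. The fallback matters: minimum EMA compliance is 5 days, so up to 14 − 5 = 9 nights could lack a reported window. State also whether a day runs midnight to midnight or wake to wake.

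Report two sensitivity analyses: sleep under the unfiltered 20-hour rule, and MVPA under an awake-wear-only rule.

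The change needs wording and a post-processing step, and no new data collection. With nine participants enrolled as of January 2026, it can be specified before analysis. The cost is that some nights now counted become missing, in a number that cannot be forecast from the document, and that the count of valid days will differ between the two outcomes.

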#### Exploratory outcomes.

Stress will be assessed at the individual level (chronic, current, and early life exposure) and at the home level (current household chaos). Chronic stress will be assessed as both stressful life events, and overall stress in the past month. First, the Brief Life Event Questionnaire will be used to assess chronic stress each 3-months (Visit 1, Visit 3, Visit 4). This questionnaire is a self-report measure to quantify presence of potentially traumatic and stressful events (e.g., close family member died, major financial crisis), and whether they still think about the event a lot, a little, or not at all [23,30]. Specifically, participants will be surveyed about the presence of each event within the last 6-months, or since they completed the questionnaire. This questionnaire has demonstrated high test-retest reliability (kappa: 0.88–1.0), and high sensitivity and specificity for the previous 6-months (0.89, 0.74, respectively) [39]. Second, recent stress in the past month will be assessed using the 10-item Perceived Stress Scale. This is a scale a questionnaire about feelings and thoughts over the last month, and has demonstrated in adults high values in metrics of validity and reliability [40]. Third, the early life exposure to stressful events, especially during critical periods of growth, may impact child development and later health [41,42]. We will assess adverse child experiences (ACEs) through 11 questions which query participants about events that happened prior to age 18 years old. These queries will be about family dysfunction (e.g., family member with mental illness, member in prison), and abuse (physical, verbal, etc.), and are adapted from the Behavioral Risk Factor Surveillance System ACE module, which is conducted nationwide in adults [43]. This scale’s validity and reliability was recently examined using measurement invariance, and demonstrated the total scoring is appropriate for analysis [44]. Total number of ACEs will be a potential mediator in analysis. Finally, the Confusion, Hubbub, and Order Scale (CHAOS) is a 15-item measure assessing disturbance, organization, and noise levels in the home. It has been validated in parents of young children to assess the home environment [29], and will be assessed at each visit.

Participants will be queried about using coping mechanisms, specifically “*What have you done to cope with your stress in the past 30-days?*” Participants have 12-options, including mindfulness practices, social support, sedentary behavior, and other options. These questions are based on the National Institutes of Health Effects of COVID-19 Outbreak – Adult Questionnaire for stressful events related to COVID-19; PhenX developed response options from crowdsourced to enable rapid response and address majority of coping practices [45,46]. Use of coping mechanisms, and specific coping mechanisms used will be exploratory variables.

Physiologic stress will be assessed through salivary cortisol. Participant will be provided with collection tubes at each visit, to collect 5-days of cortisol. Participants are asked to collect saliva on the first five days to coincide with physical activity and EMA collection. Five days was selected to correspond with other protocols and reduce participant burden [9]. Participants will be asked to collect a sample of their saliva within 1-hour of waking up, around the same time at all time points, and prior to consumption of sustenance. Participants will log their wake-up time and exact time of sample collection on a sheet and place the collection tube in a freezer until the end of the EMA protocol (~14-days), and the participant will transport the frozen items to the lab in a cold container (Freezebox, Crystal Industries, Addison, TX). These samples will then be frozen until analysis. The cortisol will be analyzed using an ELISA-based immunoassay, which has a sensitivity of 0.111ng/mL and an assay range of 0.2–10 mg/ml for saliva, and a reliable intra and inter assay prediction (0.41, 0.58, respectively) [47]. Samples collected outside of the 1-hour waking window will be removed from analysis.

Habitual dietary intake will be assessed using a food frequency questionnaire, the Diet History Questionnaire III (DHQ), at each of the visits. The DHQ is a web-based system developed by the National Cancer Institute to administer food frequency questionnaires, and has been validated in adults [48]. This food frequency questionnaire will 135 common foods and beverages they consumed over the past month, and include portion sizes. The DHQ III information will be used to calculate Healthy Eating Index 2015 (HEI). HEI is a calorie-adjusted measure based upon meeting the Dietary Guidelines for Americans, and ranges from 0–100 with a higher score indicating better healthier dietary quality [49].

Habitual food cravings will be assessed by the FCI full form, which assess the cravings for specific types of foods over the past month. The FCI is described previously in the Ecological Momentary Section, but in brief the FCI is a 28-item questionnaire queries five different subscales including high fat foods, sweets, carbohydrates/starches, fast foods, and fruits and vegetables. FCI responses are via a 5-point scale, with higher scores indicating more frequent cravings [28]. High FCI scores have been negatively associated with sleep metrics in other samples [50].

Physical Activity and sedentary behavior context will be assessed using the Nurses Health Survey for Physical Activity questionnaire, a reliable and validated questionnaire [51]. Participants will be asked based on the past year or since they last completed the questionnaire, on average how much time they spent in various activities per week and number of days they exercised. There were ten categorical responses, increasing from minutes (0, 1–4, 5–19, 20–59) to hours (1, 1–1.5, 2–3, 4–6, 7–10, and 11+). In a separate section of the questionnaire, participants were asked how many hours per week they spent sitting (options: away-from-home, watching television/ streaming [herein: screens], other), and standing/walking (options: at-work, at-home), with similar categorical responses. Responses will be multiplied by appropriate conversion factors to calculate minutes/week.

